## LIST OF ABBREVIATIONS

|           |                                                     |
|-----------|-----------------------------------------------------|
| AE        | Adverse event                                       |
| CFR       | Code of Federal Regulations                         |
| cp | Cold-passaged                                       |
| CRF       | Case report form                                    |
| CI        | Confidence interval                                 |
| CTM       | Clinical Trial Material                             |
| CRADA     | Cooperative Research and Development Agreement      |
| EDC       | Electronic data capture                             |
| F         | Fusion glycoprotein                                 |
| FDA       | US Food and Drug Administration                     |
| HIPAA     | Health Insurance Portability and Accountability Act |
| HIV       | Human immunodeficiency virus                        |
| ICH       | International Conference on Harmonisation           |
| IEC       | Independent Ethics Committee                        |
| IND       | Investigational New Drug Application                |
| IRB       | Institutional Review Board                          |
| IRE       | Immediate reportable event                          |
| MA-LRI    | Medically attended lower respiratory illness        |
| ml        | Milliliter                                          |
| mM        | Millimolar                                          |
| NIH       | National Institutes of Health                       |
| pfu       | Plaque-forming units                                |
| PID       | Participant identification number                   |
| PIV       | Parainfluenza virus                                 |
| PIV3      | Parainfluenza virus type 3                          |
| RSV       | Respiratory syncytial virus                         |
| SAE       | Serious adverse event                               |
| SMC       | Safety Monitoring Committee                         |
| SNMC      | Significant new medical condition                   |
| ts | Temperature-sensitive                               |

---

## LIST OF DEFINITIONS

|                                  |                                                                            |
|----------------------------------|----------------------------------------------------------------------------|
| MEDI-559                         | rA2cp248/404/1030ΔSH developed under a CRADA between MedImmune and the NIH |
| rA2cp248/404/1030ΔSH (NIH/Wyeth) | rA2cp248/404/1030ΔSH developed under a CRADA between Wyeth and the NIH     |

## STUDY ABSTRACT

### TITLE:

A Phase 1/2a, Randomized, Double-Blind, Placebo-Controlled Study to Evaluate the Safety, Tolerability, Immunogenicity, and Viral Shedding of MEDI-559, a Live Attenuated Intranasal Vaccine Against Respiratory Syncytial Virus in Healthy 1 to <24 Month-Old Children

### RATIONALE:

Respiratory syncytial virus (RSV) is the most important cause of viral lower respiratory tract illness in infants and children worldwide (Hall 2001). Palivizumab (Synagis®), a commercially available monoclonal antibody against the RSV F protein, prevents serious RSV disease in premature and other high-risk infants but is not indicated in healthy children. Since RSV infects and can cause disease in otherwise healthy infants, development of vaccines for the prevention of RSV disease is a public health priority (Murphy 2002).

A rA2cp248/404/1030ΔSH vaccine construct developed by the National Institutes of Health (NIH) was evaluated by Wyeth Pharmaceuticals in adults and children, including infants, under separate IND held by Wyeth. This construct will be referred to here as rA2cp248/404/1030ΔSH (NIH/Wyeth). MEDI-559, a closely related rA2cp248/404/1030ΔSH vaccine manufactured by MedImmune, is being co-developed by MedImmune and NIH under a Cooperative Research and Development Agreement (CRADA). MEDI-559 differs from the previously tested rA2cp248/404/1030ΔSH (NIH/Wyeth) vaccine by 39 silent base pair substitutions that do not cause any alterations of predicted amino acid sequence and result in no discernable phenotypic differences.

Phase 1 clinical studies were conducted by Wyeth to evaluate the safety and immunogenicity of rA2cp248/404/1030ΔSH (NIH/Wyeth) in seropositive human subjects (Karron 2005). In adults, the vaccine was safe and well tolerated but was non-immunogenic and failed to replicate. In RSV-seropositive children, rA2cp248/404/1030ΔSH (NIH/Wyeth) was well tolerated and highly restricted in replication. After vaccination,  $\geq 4$ -fold increases in antibody titers occurred rarely (15% in the highest dose group), suggesting that this vaccine is minimally infectious and minimally immunogenic in RSV experienced populations.

The safety of the vaccine was further confirmed in randomized, double-blind, placebo-controlled trials in seronegative children (Karron 2005). A total of 21 seronegative children 6-24 months of age received one dose of either  $10^{4.3}$  pfu or  $10^{5.3}$  pfu of rA2cp248/404/1030ΔSH (NIH/Wyeth). The vaccine was safe and well tolerated. Viral shedding was monitored throughout the trial in

seronegative children, and 8/8 subjects (100%) who received the higher dose ( $10^{5.3}$  pfu) shed virus compared to 8/13 (62%) of those who received  $10^{4.3}$  pfu. In summary, a dose of  $10^{5.3}$  pfu appeared to be more infectious and immunogenic than a dose of  $10^{4.3}$  pfu in this population without evidence of increased reactogenicity.

A two dose trial of rA2cp248/404/1030ΔSH (NIH/Wyeth) was performed to evaluate the safety, tolerability, viral shedding profile and immunogenicity of the vaccine candidate in young infants who are the target population for MEDI-559. A total of 32 infants 4-12 weeks of age were enrolled to receive two doses of either  $10^{4.3}$  or  $10^{5.3}$  pfu 4-8 weeks apart. The vaccine was safe and well tolerated. Shedding of vaccine virus appeared to be dose dependent with the first vaccination priming for reduced shedding after second vaccination.

These clinical data support the further development of the MEDI-559 construct as a potential RSV vaccine. The epidemiology of RSV disease, with a disproportionate burden of disease borne by infants in the first year of life, suggests that the target age group for vaccination should be very young infants ([Lee 2005](#)).

The overall objective of the clinical development program is to evaluate the safety and efficacy of MEDI-559 for the prevention of serious RSV disease in infants and young children. The trials will evaluate the MEDI-559 vaccine using an equivalent dose in the same populations that were previously studied by Wyeth. The proposed expanded Phase 1/2a study will evaluate the safety, tolerability, immunogenicity and viral shedding of three doses of MEDI-559, first in 5 to <24-month old seronegative children and then in healthy young infants not screened for baseline serostatus. This trial will confirm the clinical safety and viral shedding profile of the new clinical trial material and generate expanded safety information on this vaccine to support a subsequent Phase 2b proof-of-concept efficacy trial.

## **OBJECTIVES:**

### **Primary Objective**

The primary objective of this study is to describe the 28-day post final dose safety and tolerability of three doses of MEDI-559 at  $10^5$  FFU when administered to healthy RSV seronegative children 5 to <24 months of age and to healthy infants 1 to <3 months of age regardless of baseline serostatus.

### **Secondary Objectives**

The secondary objectives of this study are:

1. To describe the incidence and magnitude of MEDI-559 shedding after each dose
2. To evaluate the immune response generated by multiple doses of MEDI-559

3. To evaluate the genotypic and phenotypic stability of recovered vaccine virus
4. To describe the incidence of serious RSV disease in vaccinated subjects through 365 days after randomization
5. To describe the safety of MEDI-559 through 365 days post Dose 1

## DESIGN:

This is a randomized, double-blind, placebo-controlled, multi-dose, Phase 1 /2a multi-center trial to evaluate the safety, tolerability, viral shedding, immunogenicity, and genotypic and phenotypic stability of MEDI-559 in RSV seronegative infants 5 to <24 months of age and in infants 1 to <3 months of age regardless of baseline serostatus. MEDI-559 will be administered at a dose of  $10^5$  FFU on a 0, 2, 4 month schedule to two cohorts of subjects in a step-wise fashion (see Section 4.9 for cohort progression scheme). The target sample size for this study is 320 subjects, with 160 subjects 5 to <24 months of age enrolled into Cohort 1 and 160 subjects 1 to <3 months of age enrolled into Cohort 2. This design follows the population and dose level used in previous clinical trials conducted with rA2cp248/404/1030ΔSH (NIH/Wyeth) ([Karron 2005](#)).

Each cohort will be randomized 1:1 (MEDI-559 to placebo) and stratified by site. Cohort 1 will initiate dosing at  $10^5$  FFU MEDI-559. The Medical Monitor and Safety Monitoring Committee (SMC) will review blinded safety data from the first 40 subjects enrolled in Cohort 1 for the 28 days following administration of the first dose of vaccine. Safety data for review includes solicited symptoms, adverse events (AEs), serious adverse events (SAEs), and medically attended lower respiratory illness (MA-LRIs). The SMC may also choose to review data by A/B grouping (treatment A vs. treatment B) or by unblinded grouping (MEDI-559 vs. placebo). If no safety concerns are noted, Cohort 2 will initiate dosing at  $10^5$  FFU MEDI-559.

Enrollment into Cohort 2 will be halted after approximately 40 subjects have been randomized. The Medical Monitor and SMC will review available blinded safety data through 28 days post Dose 1 for these 40 subjects. If no safety concerns are noted, the remainder of Cohort 2 will be enrolled.

Subjects will be followed for 365 days after randomization. This will standardize the follow-up period for all subjects across all sites and locations globally, regardless of local RSV epidemiology, and it ensures that all subjects are followed through a full RSV season after dosing.

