## 2.3 Overview

This is a randomized, double-blind, placebo-controlled, multi-dose, Phase 1/2a multi-center trial to evaluate the safety, tolerability, viral shedding, immunogenicity, and genotypic and phenotypic stability of MEDI-559 in RSV seronegative infants 5 to <24 months of age and in infants 1 to <3 months of age regardless of baseline serostatus. MEDI-559 will be administered at a dose of  $10^5$  FFU on a 0, 2, and 4 month schedule to two cohorts of subjects in a step-wise fashion (see Section 4.9 for cohort progression scheme). The target sample size for this study is 320 subjects, with 160 subjects 5 to <24 months of age enrolled into Cohort 1 and 160 subjects 1 to <3 months of age enrolled into Cohort 2. This design follows the population and dose level used in previous clinical trials conducted with rA2cp248/404/1030ΔSH (NIH) ([Karron 2005](#)).

Each cohort will be randomized 1:1 (MEDI-559 to placebo) and stratified by site. Cohort 1 will initiate dosing at  $10^5$  FFU MEDI-559. The Medical Monitor and Safety Monitoring Committee (SMC) will review blinded safety data from the first 40 subjects enrolled in Cohort 1 for the 28 days following administration of the first dose of vaccine. Safety data for review includes solicited symptoms, adverse events (AEs), serious adverse events (SAEs), and medically attended lower respiratory illness (MA-LRIs). The SMC may also choose to review data by A/B grouping (treatment A vs. treatment B) or by unblinded grouping (MEDI-559 vs. placebo). If no safety concerns are noted, Cohort 2 will initiate dosing at  $10^5$  FFU MEDI-559. Enrollment into Cohort 2 will be halted after approximately 40 subjects have been randomized. The Medical Monitor and SMC will review available blinded safety data through 28 days post Dose 1 for these 40 subjects. If no safety concerns are noted, the remainder of Cohort 2 will be enrolled.

The study will be conducted globally in multiple sites with dosing throughout the year. All subjects will be followed through 365 days after randomization to ensure that each subject has been followed through an RSV season.

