## **3.2 Randomization**

### **3.2.1 Subject Randomization Procedures and Treatment Allocation**

Subjects will be screened by investigators to assess eligibility for entry into the study. A master log will be maintained of all screened subjects. When a subject arrives in the clinic for the Study Day 0 visit (day of initial study vaccination), the investigator will confirm that the subject meets all eligibility criteria. Subjects whose legal representative has signed an informed consent at screening and who meet eligibility criteria will be randomized into the study.

On the first day of dosing, subjects whose legal representative signed an informed consent and who meet all eligibility criteria (including re-assessment of all eligibility criteria on the day of dosing) will be randomized. For each cohort, subjects will be randomized at a 1:1 ratio (MEDI-559 to placebo) and randomization will be stratified by site. Subjects within each cohort for whom their legal representative has provided written informed consent for the collection of additional samples may have an additional three blood samples collected for immunogenicity evaluations. Randomization will be managed centrally through an interactive voice response system (IVRS).

A participant is considered to be randomized into the study upon assignment of a participant identification number (PID). All subjects entered into the study will be assigned a unique PID. Once assigned, the PID will be maintained by the same subject throughout the trial.

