| Study vaccine administration e                          |           | X                |                   |                |                   | X                |                |                |                   | X                |                |                |                |                  |                |                           |
| Nasal wash specimen                                                | X         |                  | X                 | X              | X                 |                  | X              | X              | X                 |                  | X              | X              | X              |                  | X f |                           |
| Solicited symptoms, AEs, & concomitant medication use g |           | ↔                |                   |                |                   | ↔                |                |                |                   | ↔                |                |                |                |                  | X i |                           |
| MA-LRIs, SAEs, SNMCs                                               |           | ↔                |                   |                |                   |                  |                |                |                   |                  |                |                |                |                  |                | X                         |

Scheduled clinic visits to occur at screening (2-21 days prior to Dose 1); on Day 0 (Dose 1 administration), 56 days ( $\pm 8$  days) post Dose 1 (Dose 2 administration), and 56 days ( $\pm 8$  days) post Dose 2 (Dose 3 administration); and at 7-10, 12-18, and 28-34 days after each dose (blood and/or nasal specimen collection). Telephone contacts will occur on a monthly basis after the subject has completed the final scheduled clinic visits to assess the occurrence of MA-LRIs, SAEs, and SNMCs. A final telephone contact is scheduled for 365-379 days post final dose.

- a. Perform prior to dosing.
- b. Verify initial eligibility (Dose 1, Sections 3.1.1 and 3.1.2) and continuing eligibility (Dose 2 and Dose 3, Sections 4.7 and 4.8).
- c. Update screening medical history, physical exam (including body weight), and current medication use (any new findings since screening).

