### **3.5 Subject Evaluation Methods**

#### **3.5.1 Safety Evaluations**

Each subject's legal representative will be given a thermometer and daily assessment worksheets with instructions. Beginning on the evening of each study vaccine dosing and for the following 28 days (0-28 days post each dose), the subject's legal representative will record daily temperatures (axillary route preferred), the occurrence of solicited symptoms, other AEs, and concomitant medication use. The temperature should be taken at approximately the same time each day. If more than one temperature is taken on the same day using the same route, the highest

value should be recorded. Study staff will collect and review study worksheet information and resolve any discrepancies at study site visits.

AEs that are ongoing at 28 days after any dose will be followed until resolution or stabilization by weekly telephone contacts for up to 6 additional weeks and, if needed, by monthly contacts through 365 days post randomization.

The study staff will contact the subject's legal representative by telephone on a monthly basis after the subject has completed the final scheduled clinic visits to assess the occurrence of SAEs, MA-LRIs and SNMCs. A final telephone contact is scheduled for 365 days after randomization. The subject's legal representative will be instructed to notify study personnel at any time during the study if the subject is hospitalized or has any unusual, alarming, or unexpected events.

Solicited symptoms, AEs, MA-LRIs, SAEs, and SNMCs and concomitant medication use will be documented in the subject's record and entered into the CRFs.

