#### **4.6 Safety Management During the Study**

The MedImmune Medical Monitor has primary responsibility for the ongoing medical review of safety data throughout the study. This includes immediate review of SAEs, MA-LRIs, and Grade 3/Grade 4 AEs, which are all immediately reportable events, and timely review of other AEs reported during the study. Monthly data listings of preliminary safety data will be provided for review of events occurring within 28 days of any study dose. The Medical Monitor will determine if the threshold has been met for immediate review of Grade 3/Grade 4 AEs (see Section 4.8), SAEs, and MA-LRIs by the Unblinded Safety Physician and Safety Biostatistician (a clinical trial specialist and statistician not directly associated with the conduct of the study). Once the threshold has been met for review of an event(s), the Unblinded Safety Physician and Safety Biostatistician have primary responsibility for assessment of Grade 3/Grade 4 AEs, MA-LRIs, and SAEs to determine whether stopping rules have been met such that events must be reviewed by the SMC (see below). At their discretion, they may review blinded or unblinded data in listings or tables, including virology data.

Consistent with protocol Section 4.1.6 (Study Reporting Period for Enhanced Disease Surveillance), the Medical Monitor has responsibility for ongoing review of MA-LRI events through 365 days post dosing to assess the need for review by the Unblinded Physician and Safety Biostatistician. For this purpose, all MA-LRI hospitalizations or deaths (whether occurring within or later than 28 days post dosing) will be attributed, hypothetically, to the vaccine arm, and if this would result in a statistical imbalance in these events, the Unblinded Physician and Safety

Biostatistician will review events in blinded or unblinded fashion in conjunction with RSV testing and event severity data to determine if imbalance has occurred. The Medical Monitor can also request review by the Unblinded Physician and Safety Biostatistician if concerns arise regarding potential imbalance in rates of MA-LRI events or severity of MA-LRI events.

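### Follow-up to 365 days after randomization does not ensure every child a full RSV season after dosing, and the Table 1 text puts the final contact 112 to 126 days later than the rest of the protocol

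*Protocol*

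**What the plan says.** The Abstract (Design) states "Subjects will be followed for 365 days after randomization" and adds that "it ensures that all subjects are followed through a full RSV season after dosing". Section 2.3 is milder: "All subjects will be followed through 365 days after randomization to ensure that each subject has been followed through an RSV season". It also says "The study will be conducted globally in multiple sites with dosing throughout the year".

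Randomization takes place on Study Day 0, the day of Dose 1 (Section 3.2.1). Section 3.4 places Dose 2 at 56 ± 8 days after Dose 1, and Dose 3 at 56 ± 8 days after Dose 2.

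The end of follow-up is stated as follows:

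- Section 3.5.1: "A final telephone contact is scheduled for 365 days after randomization".
- Table 1, footnote h: MA-LRIs, SAEs and SNMCs are collected to 365 days after randomization. Sections 3.6, 4.1.5, 4.1.6 and 4.2.2 use the same anchor.
- Text under Table 1: "A final telephone contact is scheduled for 365-379 days post final dose".
- Section 4.6: "the Medical Monitor has responsibility for ongoing review of MA-LRI events through 365 days post dosing", with no dose named. The paragraph that follows in the same section counts from randomization.

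**The concern.** Secondary objective 4 (serious RSV disease), the secondary endpoint on immunologic enhancement and the Section 4.1.6 comparison of RSV-related hospitalization or death are informative only to the extent that vaccinated children meet wild-type RSV. The Abstract tells the reader that every child is observed through a complete season after dosing. Sections 4.1.6 and 4.6 build on that idea, since the response to a signal is follow-up through an additional season.

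The vaccine is a three-dose series lasting nearly four months, and children start it at any time of year. If the season claim is taken at face value, a null enhanced-disease result would be credited with more exposure after the series than was observed. This study is meant to support a later efficacy trial, so the reading of a null result matters.

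The two dates for the final contact are a separate matter. They are a plain inconsistency in operative text, not a remnant in the change summary.

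**Working it through.** **Inputs from the protocol.** Randomization = Dose 1 = Day 0 (Section 3.2.1). Dose intervals are 56 ± 8 days (Section 3.4). If Dose 2 is missed, Dose 3 is given 96 to 120 days after Dose 1 (Section 4.7). Follow-up ends on Day 365 (Abstract, Sections 2.3 and 3.5.1).

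**Assumed, because the protocol does not give it.** One annual season of fixed length L, tried from 90 to 210 days, and randomization dates uniform over the year. Under uniform enrolment the calendar position of the season does not matter, only its length.

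**1. Day of Dose 3.** Nominal 56 + 56 = 112. Earliest 48 + 48 = 96. Latest 64 + 64 = 128.

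**2. Follow-up left after Dose 3.** 365 − 112 = 253 days, about 8.3 months. Range 365 − 128 = 237 to 365 − 96 = 269. If Dose 2 is missed: 365 − 120 = 245 to 365 − 96 = 269.

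**3. Share of children with one complete, unbroken season.** The protocol gives no figure beyond its claim that all children have one. For an observation period of W days, an unbroken season fits for W − L + 1 of the 365 possible enrolment days, so the share is (W − L + 1)/365. For example, with W = 253 and L = 150 it is 104/365 = 28%.

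| Season length L (days) | After Dose 3, W = 253 | Range, W = 237 to 269 | From Dose 1, W = 365 |
|---|---|---|---|
| 90 | 45% | 41% to 49% | 76% |
| 120 | 37% | 32% to 41% | 67% |
| 150 | 28% | 24% to 33% | 59% |
| 180 | 20% | 16% to 25% | 51% |
| 210 | 12% | 8% to 16% | 43% |

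Enumerating all 365 enrolment days gives the same shares.

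**4. Worst case.** The first 112 days can all fall in season, so the fewest season days left after Dose 3 is L − 112, or 0 if that is negative. This gives 0 days for L = 90, 8 for L = 120 and 38 for L = 150.

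**5. Average.** Under the same assumptions, 253/365 = 69% of season days fall after Dose 3.

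**6. From Dose 1.** A 365-day period contains each calendar date once, so all L season days are observed in total. A child enrolled mid-season gets them as the end of one season and the start of the next.

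**7. Gap between the two final contacts.** The text under Table 1 gives Day 112 + 365 = 477 to 112 + 379 = 491, against Day 365. The gap is 112 to 126 days at nominal timing. Across the dosing windows it runs from 96 + 365 − 365 = 96 to 128 + 379 − 365 = 142 days.

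**The case against.** **The protocol counts from first exposure.** Objective 5 runs to 365 days after Dose 1, and MA-LRI reporting starts after the initial vaccination. On that basis every season day is observed. This stands as far as it goes, and it is why the design cannot be said to miss the season. It does not support the Abstract's clause, which speaks of a full season after dosing when dosing lasts to about Day 112. Even from Dose 1, a single unbroken season is not assured.

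**Only the Abstract makes the strong claim.** This is correct. Section 2.3 speaks of an RSV season, without calling it full and without placing it after dosing. It needs alignment only.

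**The percentages rest on outside assumptions.** This is also correct. Season length is not in the protocol, entry is staged with a pause in Cohort 2, and a global trial has more than one season pattern. The percentages are illustrations. That the guarantee fails is not sensitive to length within the range tested.

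**The date conflict is an isolated slip.** Largely so. Randomization is the anchor in nearly every section, and Section 4.6 says its review is consistent with Section 4.1.6, which uses randomization. A reader might infer that sites will stop collecting events at different times. Sections 4.1.5 and 4.2.2 fix the reporting periods explicitly, so the documents do not support that.

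**Bias.** A reader might also infer a biased comparison. Randomization is 1:1 within site, so both arms share the same calendar exposure. The primary endpoints, which concern safety to 28 days after dosing, are untouched.

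**Conclusion.** The point holds in a limited form. Follow-up to Day 365 does not ensure, for all children, a full RSV season after dosing, because about 253 days (237 to 269) remain after Dose 3 under year-round dosing. That follows from the protocol's own dates for any season of the lengths tried. How many children are affected depends on the assumed season length and uniform enrolment. At every length tried, fewer than half would have one unbroken season after Dose 3, although on average 69% of season days still fall after it.

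It would go too far to say that the design cannot deliver a season. Many children will have a complete one, and all have 12 calendar months from Dose 1. The consequence is over-reading of a null enhanced-disease result.

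The second part needs no assumption. The final contact in the text under Table 1 conflicts with Section 3.5.1 and with the collection period in the same table's footnote h, by 112 to 126 days at nominal timing. The Section 4.6 wording is ambiguous rather than clearly different.

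**What to change.** 1. **One anchor.** Change the text under Table 1 and the Medical Monitor sentence in Section 4.6 to 365 days after randomization, as used elsewhere.
2. **Season claim.** Replace the Abstract clause with a statement that follow-up covers 12 calendar months from Dose 1 and about 8 months after Dose 3. Align Section 2.3.
3. **Exposure.** Report in-season person-time after the final dose, by arm and cohort, beside the RSV-associated MA-LRI and hospitalization results. Define the season for each region before unblinding.

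Items 1 and 2 cost only wording. Item 3 costs one summary table from dose and contact dates, plus the season definition.

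Extending follow-up to 365 days after the final dose is an option for the sponsor, not a required correction. It would add about four monthly calls per child (112/30 ≈ 3.7; 320 × 4 = 1,280 calls). It would also add illness visits and nasal washes, and would change consent, inclusion criterion 8 and the completion definition in Section 3.6. Every calendar date would then be covered once after the series, but one unbroken season would still not be guaranteed: 76%, 59% and 43% of children for seasons of 90, 150 and 210 days. The season wording needs correcting either way.
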